# Stereoptic serious games as a visual rehabilitation tool for individuals with a residual amblyopia (AMBER trial): a protocol for a crossover randomized controlled trial

**DOI:** 10.1186/s12886-023-02944-y

**Published:** 2023-05-17

**Keywords:** Amblyopia, Child, Binocular stimulation, Dichoptic stimulation, Optical treatment, Refractive correction, Virtual reality, Stereovision, Visual attention, Kinematics, Motor control, Electroencephalography

## Abstract

**Background:**

Amblyopia is the most common developmental vision disorder in children. The initial treatment consists of refractive correction. When insufficient, occlusion therapy may further improve visual acuity. However, the challenges and compliance issues associated with occlusion therapy may result in treatment failure and residual amblyopia. Virtual reality (VR) games developed to improve visual function have shown positive preliminary results. The aim of this study is to determine the efficacy of these games to improve vision, attention, and motor skills in patients with residual amblyopia and identify brain-related changes. We hypothesize that a VR-based training with the suggested ingredients (3D cues and rich feedback), combined with increasing the difficulty level and the use of various games in a home-based environment is crucial for treatment efficacy of vision recovery, and may be particularly effective in children.

**Methods:**

The AMBER study is a randomized, cross-over, controlled trial designed to assess the effect of binocular stimulation (VR-based stereoptic serious games) in individuals with residual amblyopia (*n* = 30, 6–35 years of age), compared to refractive correction on vision, selective attention and motor control skills. Additionally, they will be compared to a control group of age-matched healthy individuals (*n* = 30) to account for the unique benefit of VR-based serious games. All participants will play serious games 30 min per day, 5 days per week, for 8 weeks. The games are delivered with the Vivid Vision Home software. The amblyopic cohort will receive both treatments in a randomized order according to the type of amblyopia, while the control group will only receive the VR-based stereoscopic serious games. The primary outcome is visual acuity in the amblyopic eye. Secondary outcomes include stereoacuity, functional vision, cortical visual responses, selective attention, and motor control. The outcomes will be measured before and after each treatment with 8-week follow-up.

**Discussion:**

The VR-based games used in this study have been conceived to deliver binocular visual stimulation tailored to the individual visual needs of the patient, which will potentially result in improved basic and functional vision skills as well as visual attention and motor control skills.

**Trial registration:**

This protocol is registered on ClinicalTrials.gov (identifier: NCT05114252) and in the Swiss National Clinical Trials Portal (identifier: SNCTP000005024).

## Background

Amblyopia is one of the most common developmental vision disorders in children, affecting 1–5% of the population in developed countries [1, 2]. It arises from abnormal visual experience in early life. Amblyopia is most commonly caused by one or a combination of (i) significant refractive error (unilateral amblyopia caused by asymmetric error, or bilateral amblyopia caused by bilateral high refractive error); (ii) strabismus; or (iii) early visual deprivation (usually congenital causes) [3]. Besides significantly reduced visual acuity, amblyopic patients exhibit binocular dysfunction that may translate into reduced binocular reading speed [4], selective attention impairment [5], or motor control skills deficits [6].

Amblyopia is typically diagnosed around the age of 3–5 years, and the initial treatment consists of refractive correction [7]. If this measure fails to produce the desired outcome after 3 months, which is similar visual acuity between both eyes, occlusion therapy is commonly used [8]. This involves patching the dominant/healthy eye for 2–6 h/day, depending on the severity of the amblyopia, every day for several months up to years [9]. However, occlusion therapy carries the risk of reverse amblyopia and new strabismus by overtreatment [10]. In addition, poor adherence to the occlusion regimen is a common problem in pediatric populations (ranging from 49 to 87%), resulting in treatment failure [11] and residual amblyopia (i.e., reduced visual acuity and stereopsis that will persist into adulthood). Children with residual amblyopia may develop social and emotional problems (e.g., low self-esteem, bullying), which may affect their quality of life and that of their families [12, 13]. Therefore, it is important to seek suitable alternatives to the occlusion therapy.

Aiming to increase compliance and treatment effectiveness, serious games delivered on tablets have recently been developed (serious games are games used for purposes other than mere entertainment [14]). More specifically, these games focused on binocular stimulation by using dichoptic images, where the contrast level of the image to the fellow eye is reduced to encourage binocular integration of complementary images, and as such to balance cortical input and overcome interocular suppression. Such dichoptic stimulation delivered on tablets seems to effectively improve visual acuity [15–19] and might be superior to occlusion therapy [15, 20]. Nevertheless, the additional recovery of stereovision (3D vision) seems to require further ingredients in the training. Three studies have shown an improvement in stereovision in adults with amblyopia when using one game in a Virtual Reality (VR) environment [21–24], suggesting that a VR-based training providing 3D cues and rich feedback may better target improvement in stereovision in both strabismic and anisometropic type of amblyopia, improving also treatment compliance [25]. However, these preliminary studies in adults delivered the VR in a lab environment and with only one or two games. A recent review showed that binocular perceptual learning and dichoptic videogames result in improved stereovision in adults with strabismus, compared to the null results seen with monocular versions of such stimulation [26]. This review gathers data from almost 100 adults with amblyopia and provides three conclusions: (1) more patients with anisometropic amblyopia improve compared to the strabismic type, (2) many more patients with strabismus have not measurable stereopsis before and after the training, compared to the anisometropic type, and (3) both types of amblyopia show improvements in stereopsis, regardless of their baseline stereoacuity, achieving stereoacuities of 140 arcsec or better. As such, we hypothesize that a VR-based training with the suggested ingredients (3D cues and rich feedback), combined with increasing the difficulty level and the use of various games in a home-based environment is crucial for treatment efficacy of vision recovery, and may be particularly effective in children.

Besides the potential improvements in visual acuity and stereovision that the VR-training may induce, we also need to target the known selective attention and motor planning deficits in children with amblyopia. The VR environment offers an enriched, immersive (depth perception, stimulation of full visual field) perceptual experience, that puts strong demands on uni- (visual) and multisensory (audiovisual) selective attention, while performing natural body movements (reaching a target, body rotation to avoid enemy) [21, 27]. Hence, a VR environment with (i) a variety of available games that increases difficulty with improvement of function (to increase compliance), (ii) games that require time constraints and a high load on divided attention (to target selective attention, as shown in adults [28]) and (iii) the opportunity to interact with the body accurately to complete the tasks (to target motor deficits, as shown in stroke survivors [29]) appears to be an optimal training to improve selective attention and motor planning deficits associated with vision problems.

In addition to assessing the effectiveness of the novel treatment, this study may provide some mechanistic insight on visual improvement by exploring the neural substrates of vision, cognitive, and motor deficits in this population. With scalp electroencephalography (EEG), we can determine changes in the cortical activity before and after an intervention, in an easy and child-friendly way. EEG has been used to understand the visual deficits [30], to depict deficits of attentional modulation in the visual cortex [31, 32] and to understand the treatment-driven plasticity [33]. To the best of our knowledge, EEG has not been used to explore the sensorimotor networks in patients with amblyopia, although these networks seems to be affected, as revealed by other brain imaging techniques (i.e., resting state magnetic resonance imaging) [34]. These preliminary results provide a rationale for using EEG in amblyopia, to explore the plasticity of the cortical networks in residual amblyopia, and its relationship with clinical changes.

This study protocol describes the setup for a Randomized Controlled Trial (RCT) comparing the effects of a personalized, VR, and home-based binocular stimulation intervention in people with residual amblyopia compared to standard care and to healthy controls. The first objective is to examine whether VR game-based interventions are not inferior to refractive correction in residual amblyopia and whether it will result in similar or better retention of the improvements. Secondly, we aim to explore whether such VR-derived improvements in the amblyopic cohort are beyond the changes we find in the control cohort. Lastly, we will study the underlying neural mechanisms of improvements by measuring brain activity and will ascertain whether such mechanisms can predict, in combination with clinical measures, treatment outcome.

This RCT will address the following research aims:a) test the efficacy of a serious game-based binocular stimulation in a VR environment in improving Best Corrected Visual Acuity (BCVA), compared to refractive correction in individuals with residual amblyopiab) test the potential VR-based benefits on clinical measures of other vision skills like stereoacuity, functional vision (i.e., reading skills), and suppression, compared to refractive correction in individuals with residual amblyopiac) test the potential benefits of VR-based training on visual and audiovisual selective attention and motor control skills, compared to refractive correction and to the control groupd) evaluate the adherence and safety of the VR-based intervention compared to standard caree) test the potential VR-based benefits on eye-related quality of lifef) test the potential VR-based benefits on cortical responses including visual, higher cognitive processes of audio-visual, and motor control skills in both cohortsg) test whether the potential VR-derived benefits on vision, attention and motor control skills in residual amblyopic patients are larger from those found in the control cohorth) identify clinical and electrophysiological factors predicting treatment response in individuals with residual amblyopia.

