## Methods I: Participants, interventions, and outcomes

### Study design

This is a single-center, evaluator-masked, non-inferiority, cross-over Randomized Controlled Trial (RCT). This study is approved by the Ethical Cantonal Board of Geneva, Switzerland (CCER N° 2021-D0090) and all methods are performed in accordance with the relevant guidelines and regulations. The protocol for this study was designed according to the SPIRIT (Standard Protocol Elements: Recommendations for Interventional Trials) 2013 Statement [35, 36]. Recruitment of participants is planned from May 2022 to December 2024. The trial will take place in the Department of Ophthalmology of the Geneva University Hospitals (Switzerland). The amblyopic cohort will take part in the cross-over design. They will be randomly assigned to take part either first in the study-intervention arm and second in the control-treatment arm, or vice versa (AB or BA), stratified according to the type of amblyopia (anisometropic, strabismic or mixed). They are not masked to the order of the received training. The age-matched control cohort will only complete the VR-based intervention.

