#### Control intervention for the control cohort

The control cohort will only undergo the VR-based intervention with the stereoscopic serious games on the Vivid Vision Home software. However, the games will not have any between-eyes image difference in terms of contrast (although those games with dichoptic stimulation will be displayed in the same way). The Smart Assist algorithm will be turned off for this cohort.

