##### Binocular vision: measurements in the Vivid Vision Home software

A Composite Depth Score estimate is measured (0–30) where 0 indicates no stereovision and 30 indicates a stereo threshold of 20 arc sec or better. Patients need to choose which of 4 circular stimuli are floating off the surface, where with each correct response the stimuli become smaller and the disparity decreases. The degree of binocular vision is estimated with a virtual Worth 4 Dot test, revealing normal vision, double vision, or suppression of left or right eye [40]. Ocular posture adjustment estimates the minimal correction needed for patient’s ocular posture in a horizontal, vertical and rotational prism is estimated in prism diopters through a Maddox rod like test [41], where the patient aligns vertical and horizontal lines with a spot or a pair of horizontal lines. Vergence is evaluated through the speed of the patient’s ability to switch between difference vergence demands is estimated in seconds as the participant is aligning a series of shapes or symbols until they make up a single line [42]. Lastly, the vergence range is the participant’s maximal horizontal and/or vertical vergence ability and is estimated in prism diopters as the participant is aligning a series of shapes or symbols until they make up a single line [42]. These tests are measured at every assessment point and are automatically performed by the software.

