### Sample size

We calculated the sample size necessary to obtain a significant difference (α = 0.05) between our treatment and refractive correction based on medium effect size (F’s Cohen = 0.25) with 80% power for a crossover design immediately after the intervention on our primary endpoint. This estimation resulted in a total sample of 24 individuals with residual amblyopia. To account for the potential dropout, we will increase the sample size by 25%, resulting in 30 individuals with amblyopia. We will additionally recruit 30 age-matched typically developing individuals to undergo the serious game VR-training. This sample will serve to account for the potential changes in vision, selective attention and motor control which are known to occur in healthy adults after a VR-training.

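### The patient-versus-healthy contrast cannot serve as a test of VR benefit in aim (c) or isolate VR's unique benefit, because the healthy cohort also plays VR and has no non-VR period

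*Protocol article*

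**What the plan says.** The healthy cohort is given an inferential role in several places of the protocol article.

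- **Abstract, Methods:** patients are compared with age-matched healthy individuals "to account for the unique benefit of VR-based serious games".
- **Background, second objective:** "we aim to explore whether such VR-derived improvements in the amblyopic cohort are beyond the changes we find in the control cohort".
- **Background, aim (c):** VR benefit on selective attention and motor control is to be tested against two comparators, refractive correction and the control group.
- **Background, aim (g):** whether VR-derived "benefits on vision, attention and motor control skills in residual amblyopic patients are larger from those found in the control" cohort.
- **Sample size:** "This sample will serve to account for the potential changes in vision, selective attention and motor control". The same sentence adds that healthy adults are known to show such changes after VR training.
- **Statistical analysis:** linear mixed models will make both comparisons, VR against refractive correction and patients against healthy controls.

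On what that cohort receives, Study design says: "The age-matched control cohort will only complete the VR-based intervention". The section on its intervention adds that "the games will not have any between-eyes image difference in terms of contrast" and "The Smart Assist algorithm will be turned off for this cohort". Allocation states that it is not randomised. Patients, by contrast, have an 8-week period of glasses alone within the crossover, and they also wear updated correction while playing.

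**The concern.** A comparator isolates the benefit of a treatment when it goes without that treatment and is otherwise alike. The healthy cohort fails on both counts. It receives VR, so the contrast subtracts whatever VR does in healthy people. It differs from the patients in population and in game version, so the contrast also picks up any cohort difference in practice, effect of glasses, regression to the mean or maturation.

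The possible errors run in both directions. A larger change in patients could be credited to VR when VR contributed nothing. A real attention or motor gain of equal size in both cohorts would look like no benefit on the control-group half of aim (c). Because aim (c) names two comparators for one benefit claim and gives neither precedence, the two can disagree with no rule for which one decides.

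**Working it through.** **Inputs from the protocol.** 30 patients and 30 controls; 24 evaluable patients before inflation (24 × 1.25 = 30); alpha 0.05. The stated calculation concerns the crossover comparison only. The protocol gives no power or effect size for the patient-versus-healthy contrast, so there is no figure of its own to reproduce here.

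**Assumptions.** Two-sided test; effects in units of the SD of change, set to 1 in both cohorts; unadjusted change scores; no carry-over in the crossover. The documents give no non-VR change and no SD, so a range is shown.

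**What each contrast estimates.** Let v be the VR effect and c the non-VR change over a period.

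- Cohort contrast: (v_pat + c_pat) − (v_healthy + c_healthy)
- Randomised contrast in patients: (v_pat + c_pat) − c_pat = v_pat

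The first equals v_pat only if v_healthy = 0 and c_pat = c_healthy. The Sample size section contradicts the first condition. Nothing in the design secures the second.

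**Cohort contrast.** Noncentral t with 2n − 2 degrees of freedom and noncentrality Δ√(n/2). For n = 30, √15 = 3.873; for n = 24, √12 = 3.464.

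| Scenario | Δ | Noncentrality, n = 30 | Rejects, n = 30 | Rejects, n = 24 |
|---|---|---|---|---|
| No VR effect, excess c in patients 0.2 | 0.2 | 0.77 | 12% | 10% |
| No VR effect, excess c in patients 0.3 | 0.3 | 1.16 | 21% | 17% |
| No VR effect, excess c in patients 0.5 | 0.5 | 1.94 | 48% | 40% |
| VR effect 0.5 in both, equal c | 0 | 0 | 5% | 5% |
| VR effect 0.5 in patients, 0.2 in healthy, equal c | 0.3 | 1.16 | 21% | 17% |
| VR effect 0.5 in patients, 0 in healthy, 0.5 more practice gain in healthy | 0 | 0 | 5% | 5% |

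**Randomised contrast.** Paired t with noncentrality v√n / √(2(1 − r)), where r is the correlation between the two period changes. For v = 0.5 and n = 30:

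- r = 0: 0.5 × 5.477 / 1.414 = 1.94, power 46%
- r = 0.5: 0.5 × 5.477 / 1 = 2.74, power 75%

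With n = 24 the power is 38% to 65%. With no VR effect it rejects 5%, whatever the patients' non-VR change.

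**A repair that does not work.** One could subtract the glasses-period change from the patients' VR change and compare the result with the controls' raw change. With no VR effect and the same practice gain p in both cohorts, the expected contrast is (p − p) − p = −p. Its standard error is √((2(1 − r) + 1)/30), which is 0.316 at r = 0 and 0.258 at r = 0.5. For p = 0.5 the absolute noncentrality is 1.58 to 1.94 and rejection is 34% to 48%. For p = 0.3 rejection is 15% to 21%, and for p = 0.2 it is 9% to 12%. Nearly all of these rejections favour the controls. The raw contrast would reject 5% in the same situation.

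**The case against.** The strongest reply has four parts.

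1. **Aim (g) asks a different question.** It asks whether patients gain more than controls. For that question, equal change in both cohorts is the right null, and 5% rejection when both gain 0.5 SD is correct test size, not lost power. This stands. A reader might infer that aim (g) is itself an invalid test; the text does not support that. The difficulty lies in the abstract's unique-benefit purpose and the control-group half of aim (c).

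2. **Benefit is already tested by randomisation.** Aims (a) and (b) use refractive correction as the only comparator, and aim (c) includes it. The second objective is worded as exploratory. This stands too. A reader might infer that the trial would announce a VR effect when VR does nothing, or would miss a real one altogether. That would require the investigators to disregard their own randomised comparison, and nothing in the protocol says they will.

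3. **The sizes are assumed.** This is correct. Patients need stable acuity over 6 months, and untreated or newly diagnosed amblyopia is excluded, so drift in acuity should be small. That criterion does not limit practice on stereo, attention or motor tasks. A reader might also infer a general ceiling on the controls' vision tests. The protocol documents a cap for one software score only, where "30 indicates a stereo threshold of 20 arc sec or better", and says nothing of how many controls would reach it.

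4. **The exact model may sit in an analysis plan that is not shown.** The form of the mixed model may well be there, and the planned adjustment for baseline acuity, stereoacuity and age may alter the figures. But the comparators and the purpose are stated in the protocol, and no model can recover a non-VR period that the healthy cohort does not have.

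**Conclusion.** The point holds for the claims that lean on the healthy cohort to show VR benefit: the purpose given in the abstract and the control-group comparator in aim (c). It also limits how the second objective and aim (g) may be read. Under the assumptions above, the cohort contrast rejects in 12% to 48% of trials with no VR effect when patients have 0.2 to 0.5 SD more non-VR change than controls. It rejects in 5% when VR helps both cohorts equally by 0.5 SD, where the randomised contrast in 30 patients has 46% to 75% power. These figures show the mechanism over a plausible range; they do not forecast what this trial will find.

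The primary acuity comparison, aims (a) and (b), and the randomised half of aim (c) are untouched. Aim (g) is sound as a question about differential response, provided that the answer is not presented as a VR effect.

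**What to change.** - State that every conclusion about VR benefit in aims (a) to (c) rests only on the randomised VR-versus-refractive-correction contrast in patients.
- In aim (c), remove the control group as a test of benefit. In the abstract, remove the unique-benefit purpose.
- Label the second objective and aim (g) as an exploratory, non-randomised comparison of change during VR between two cohorts using different game versions, and say that it does not identify a VR effect.
- Report the proportion of controls at the test limit for each bounded vision measure.
- Do not subtract the glasses-period change from the patients alone. A balanced correction would need a non-VR period in the healthy cohort, which the design does not include.

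The cost is wording and analysis labels; no new data are needed. The downside is that the healthy comparison then supports a weaker claim.
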